#### **4.5.5 Criteria for subject discontinuation**

- Any allergic reaction or AE occurs such that continued participation in the study would not be in the best interest of the subject at the discretion of the treating physician;
- Worsening of clinical conditions occurs such that continued participation in the study would not be in the best interest of the subject at the discretion of the treating physician; considered as ineffective cases;
- Subjects are free to withdraw from participation in the study at any time upon

request.

In any case, every effort must be made to determine why patients discontinued the study treatment prematurely, which may include but are not limited to poor confidence in efficacy, occurrence of AEs, SAEs, or other serious complications, worsening of symptoms such that emergent intervention is required. As for those who withdrew from participation in the study or lost to follow-up, it is essential to investigate the potential reasons via telephone or mail. Investigators should record in detail when and how the last dose was administered, the efficacy and safety parameters at and after discontinuation, the relationship between discontinuation or withdrawal and the study drug, and the potential impact of discontinuation cases on the final conclusion of the study. Moreover, case report form (CRF) of withdrawal/dropout cases should also be completed and their original data should also be documented and stored in a secure manner.

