### 6.2 Efficacy parameters

The primary efficacy endpoint of this study is:

- Proportions of patients who were angina-free.

Angina-free was defined as the responses of patients' anginal symptoms were "none" on the Quantification Score of Angina Pectoris (see page 19 for details) including three dimensions (attack frequency, severity and duration of angina) over the 20-weeks treatment phase. The Quantification Score of Angina Pectoris comprising questions investigating the patients' anginal symptoms was administered by the physician in charge of the study at 2, 4, 6, 8 and 20 weeks in each center.

- Proportion of effective electrocardiogram (ECG) improvement.

The effective ECG improvement was defined as a standard 12-lead ECG returns to normal(or within the normal range) according to the International Society and Federation of Cardiology/World Health Organization after 20-weeks long term treatment. The ECG was performed at 0,8, and 20 weeks during treatment.

Secondary efficacy endpoints are:

- Change from baseline in weekly average frequency of self-reported angina episode over the 20-weeks treatment phase.
- Weekly average nitroglycerin consumption rate at week 8 and week 20.

Throughout the study, patients recorded the occurrence of anginal attacks and the number of nitroglycerin use on diary cards and the study staff at each clinical site reviewed the angina and nitroglycerin use cards with the patient at each study visit(2, 4, 6, 8 and 20 weeks) to ensure accuracy.

- Change from baseline in 5 dimensions of the Seattle Angina Questionnaire (SAQ) and the proportions of patients who were clinical significance at week 8 and week 20.

The SAQ is a disease-specific functional status measure that was developed to quantify the physical and emotional effects of CAD[6].Each SAQ dimension (anginal frequency, physical limitation, anginal stability, disease perception, and treatment satisfaction) was scored on a scale of 0 to 100 and the clinical significance was defined as a difference of 8 points or more on the physical-limitation scale, 25 or more on the angina-stability scale, 20 or more on the angina-frequency scale, 12 or more on the treatment-satisfaction scale, and 16 or more on the quality-of-life scale[7].Patients will complete the SAQ at 0,8, and 20 weeks.

- Change from baseline in the blood stasis syndrome and the proportion of patients who had significant syndrome improvement.

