Blood stasis syndrome which a common syndrome of chronic stable angina in TCM including the following symptoms: angina, choking sensation in the chest, palpitation, dark purple lips, ecchymosis on the tongue, and fine-choppy pulse.The syndrome score was assessed by using the Quantification score of TCM syndrome(with higher scores indicating higher severity, see page20 for details)and administered by the physician in charge of the study at 2, 4, 6, 8 and 20 weeks in each center.

The significant syndrome improvements defined as clinical signs and symptoms have been greatly improved, and decrease in syndrome score  $\geq 70\%$ [3].

- Change from baseline in ECG exercise test (the first 1/3 of patients included at each site) performed at 0 and 8 weeks.

Investigators should be aware of the contraindications to exercise test, and patients should be closely monitored during the test to ensure his/her safety, including ECG, BP, and angina.

- Change from baseline in serum lipid: total cholesterol, triglyceride, HDL cholesterol, and LDL cholesterol, measured at 0 and 8 weeks during treatment.
- Related signs: heart rate, rhythm, murmur, and BP, recorded before and after Treatment.
- Accompanying symptoms after treatment: fatigue, shortness of breath, aversion to cold, cold extremities and etc. (recorded as “yes” or “no”).

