## **7 EFFICACY EVALUATION**

### **7.1 Criteria for overall efficacy evaluation**

- Markedly effective: main symptoms like angina disappear or almost disappear, and ECG returns to normal (or within the normal range);
- Effective: main symptoms like angina and ECG features have been improved;
- Ineffective: main symptoms like angina and ECG features remain unchanged;
- Worsening: main symptoms like angina and ECG features become worse.

If the changes in main symptoms are inconsistent with those in ECG features, that of lower efficacy shall prevail.

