### **7.2 Evaluation of angina changes**

The evaluation of angina changes should be based on the quantification score of angina pectoris:

- Markedly effective: angina symptoms disappear or almost disappear, and decrease in angina score  $\geq 70\%$ ;
- Effective: attack frequency, severity and duration of angina have been greatly improved, and decrease in angina score  $\geq 30\%$  but  $< 70\%$ ;
- Ineffective: angina symptoms remain unchanged, and decrease in angina score

<30%;

- Worsening: angina symptoms become worse, and decrease in angina score <0.

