## 7.6 Use of nitroglycerin

- Withdrawal: complete withdrawal after treatment;
- Dose reduction: the number of doses decreased at least 50% after treatment;
- Unchanged: the number of doses decreased less than 50% after treatment.

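### Graded efficacy rules for nitroglycerin use and for patients stopped for worsening misplace deterioration or conflict; the SAQ threshold lacks a sign (secondary and graded outcomes only)

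*Protocol*

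**What the plan says.** **Nitroglycerin (Protocol 7.6).** There are three grades. The top one is complete withdrawal. The others are "Dose reduction: the number of doses decreased at least 50% after treatment" and "Unchanged: the number of doses decreased less than 50% after treatment". No grade for increased use follows. Use of nitroglycerin is among the efficacy measures named in the objectives (section 2).

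**Patients stopped for worsening (Protocol 4.5.5).** Where the treating physician judges that worsening makes continued participation unsuitable, the patient's outcome is fixed by the words "at the discretion of the treating physician; considered as ineffective cases".

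**Four-grade scales (Protocol 7.1 to 7.5).** Each scale runs Markedly effective, Effective, Ineffective, Worsening. Ineffective is described throughout as no change. Section 7.1 adds below it "Worsening: main symptoms like angina and ECG features become worse", and section 7.2 adds "Worsening: angina symptoms become worse, and decrease in angina score <0". In 7.2 and 7.3 the score band for Ineffective is a decrease below 30%, with no lower limit.

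**SAQ (Protocol 6.2).** A secondary endpoint is "the proportions of patients who were clinical significance at week 8 and week 20". It is defined by the statement that "the clinical significance was defined as a difference of 8 points or more on the physical-limitation scale", followed by limits of 25, 20, 12 and 16 points for the other scales. The 16-point limit is attached to a quality-of-life scale, whereas the list of dimensions just before it names disease perception.

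**The concern.** A graded outcome should place every patient in exactly one grade, and a patient who gets worse should not share a grade with one who did not change. Section 7.6 has no place for increased use. Section 4.5.5 gives patients stopped for worsening a grade that section 7 reserves for no change, one step above Worsening. The overlapping bands in 7.2 and 7.3 leave the split between the two lowest grades to the analyst.

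At stake is the content of the graded tables and, where grades are compared as ordinal data, the ranks themselves. Section 11.2 names a rank sum test for ordinal categorical data. The SAQ point is smaller: a responder threshold without a direction leaves the derivation to be inferred, while the syndrome responder in the same section does state one ("The significant syndrome improvements defined as clinical signs and symptoms have been greatly improved, and decrease in syndrome score", with a 70% limit).

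**Working it through.** The protocol gives no figure to reproduce here. The check applies the rules as written to example patients.

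**1. Nitroglycerin, section 7.6.** Percentage decrease = 100 × (baseline − after) / baseline.

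| Doses, baseline to after | Decrease | Grade under 7.6 |
|---|---|---|
| 4 to 0 | 100% | Withdrawal |
| 4 to 2 | 50% | Dose reduction |
| 4 to 3 | 25% | Unchanged |
| 4 to 4 | 0% | Unchanged |
| 4 to 8 | −100% | Unchanged |
| 4 to 12 | −200% | Unchanged |

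If a rise is held not to be a decrease at all, the last two rows have no grade. Either way the scale fails for these patients. With zero doses at baseline the percentage is undefined, so the grades do not apply to patients who were not using nitroglycerin.

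**2. Score bands, sections 7.2 and 7.3.**

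| Decrease in score | Bands met |
|---|---|
| 80% | Markedly effective |
| 50% | Effective |
| 10% | Ineffective |
| 0% | Ineffective |
| −10% | Ineffective and Worsening |
| −50% | Ineffective and Worsening |

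Every negative decrease meets both score conditions. Only the symptom wording separates the two grades.

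**3. Section 4.5.5 against section 7.** Take patient A, stopped for worsening with a score 50% above baseline, and patient B, who completes with a score 10% above baseline. Under 4.5.5, A is Ineffective. Under 7.2, taking its Worsening clause, B is Worsening. A therefore ranks above B although A deteriorated more. Section 11.1.1 carries the last observation forward for non-completers, so A's own last score would point to Worsening while 4.5.5 says Ineffective. In an effective/not-effective split both are failures and nothing changes.

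**4. SAQ, section 6.2 (illustration only).** The protocol gives no SAQ mean or SD. Assume normally distributed changes, positive = improvement, SD 20, mean +5 in control and +10 in the trial group. The threshold is 8 points on physical limitation.

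- Control: P(≥ 8) = 1 − Φ(0.15) = 0.4404; P(≤ −8) = Φ(−0.65) = 0.2578; either direction 0.6982.
- Trial: P(≥ 8) = 1 − Φ(−0.10) = 0.5398; P(≤ −8) = Φ(−0.90) = 0.1841; either direction 0.7239.
- Difference, improvement only: 0.5398 − 0.4404 = 0.0994, or 9.9 points.
- Difference, either direction: 0.7239 − 0.6982 = 0.0257, or 2.6 points.

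With the same means, SD 15 gives 13.2 against 5.4 points, and SD 25 gives 8.0 against 1.4.

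**The case against.** The strongest reply is that little turns on these rules, and much of it stands.

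- Neither primary endpoint uses them. Angina-free status rests on frequency, severity and duration, and the ECG endpoint on return to normal.
- A reader might infer that deteriorating patients become responders. Sections 7.6 and 4.5.5 do not support that: Unchanged and Ineffective are both non-response.
- A reader might infer that harm is hidden. It is not. The listed nitroglycerin endpoint in 6.2 is weekly average consumption, where a doubling shows in full. Frequency and dose of nitroglycerin also enter the angina score (4.3.1), and worsening of pre-existing conditions is reportable as an adverse event (8.2.1).
- The word ineffective in 4.5.5 can be read as a plain treatment-failure rule. Section 11.2 lists the rank sum test generically and ties it to no particular four-grade scale.
- A reader might infer that an SAQ loss counts as success and that most of the treatment difference disappears. The text omits a sign but never says that losses count. The threshold belongs to a change-from-baseline efficacy endpoint, so improvement is the natural reading.
- The two names for the fifth SAQ dimension are a naming mismatch: the other four limits match their scales by name.

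What the reply does not remove is that 7.6 has no correct grade for increased use, that 4.5.5 and section 7 disagree, and that two score bands overlap. These are definitions the protocol itself fixes, not details it leaves to a statistical analysis plan.

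**Conclusion.** The point holds as a set of misclassifying or conflicting definitions confined to secondary and graded outcomes.

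- **Section 7.6** has a gap: any increase is Unchanged or ungraded. This follows from the text without assumptions.
- **Section 4.5.5 against 7.1 to 7.5** is a contradiction about outcome grade, and the 7.2 and 7.3 score bands overlap for every negative decrease. It affects a result only if the four grades are compared by ranks. Its size depends on how many patients are stopped for worsening, which the protocol does not give.
- **The SAQ wording** needs a minor clarification. The fall from 9.9 to 2.6 points is an illustration under assumed means, SD and normality, and arises only if the unsigned wording is applied literally. It is not an estimate of what this trial would lose.

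The primary analyses and the sample size are unaffected.

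**What to change.** 1. **Section 7.6:** add a grade *Increased* (more doses than at baseline), limit Unchanged to a decrease of 0 to below 50%, and apply the grades only to patients who used nitroglycerin at baseline.
2. **Sections 4.5.5, 7.1 to 7.5 and 11.1.1:** reconcile them so that a patient discontinued for worsening is classified as Worsening on the four-grade outcome scales. This concerns the outcome grade only and leaves the rule for stopping treatment as it is.
3. **Sections 7.2 and 7.3:** bound Ineffective at a decrease of 0 to below 30%, so that it no longer overlaps Worsening.
4. **Section 6.2, SAQ:** state that each limit means improvement from baseline, say which direction of the score is improvement, and use one name for the fifth dimension.

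The cost is wording and derivation code. No new data, visits or patients are needed. Some graded tables may look less favourable because patients move from Unchanged or Ineffective to a lower grade.

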## **7 EFFICACY EVALUATION**

### **7.1 Criteria for overall efficacy evaluation**

- Markedly effective: main symptoms like angina disappear or almost disappear, and ECG returns to normal (or within the normal range);
- Effective: main symptoms like angina and ECG features have been improved;
- Ineffective: main symptoms like angina and ECG features remain unchanged;
- Worsening: main symptoms like angina and ECG features become worse.

If the changes in main symptoms are inconsistent with those in ECG features, that of lower efficacy shall prevail.

### **7.2 Evaluation of angina changes**

The evaluation of angina changes should be based on the quantification score of angina pectoris:

- Markedly effective: angina symptoms disappear or almost disappear, and decrease in angina score  $\geq 70\%$ ;
- Effective: attack frequency, severity and duration of angina have been greatly improved, and decrease in angina score  $\geq 30\%$  but  $< 70\%$ ;
- Ineffective: angina symptoms remain unchanged, and decrease in angina score

<30%;

- Worsening: angina symptoms become worse, and decrease in angina score <0.

### **7.3 Evaluation of syndrome changes**

The evaluation of syndrome changes should be based on the quantification score of the TCM syndrome:

- Markedly effective: clinical signs and symptoms have been greatly improved, and decrease in syndrome score  $\geq 70\%$ ;
- Effective: clinical signs and symptoms have been somewhat improved, and decrease in syndrome score  $\geq 30\%$  but  $< 70\%$ .
- Ineffective: clinical signs and symptoms remain unchanged, and decrease in syndrome score  $< 30\%$ ;
- Worsening: clinical signs and symptoms become worse, and decrease in syndrome score  $< 0$ .

The dynamic changes in the phenotypic group should also be assessed.

### **7.4 Evaluation of ECG changes**

- Markedly effective: ECG returns to normal (or within the normal range);
- Effective: reversion of S-T segment depression  $\geq 0.05\text{mV}$  but still remains out of the normal range, improvement in deep T wave inversions ( $\geq 25\%$ ) or transformation of flat T wave into upright T wave, and improvement in atrioventricular or intraventricular block;
- Ineffective: ECG features remain unchanged;
- Worsening: aggravation of S-T segment depression  $\geq 0.05\text{mV}$ , deeper T wave inversions ( $\geq 25\%$ ) or transformation of upright T wave into flat T wave or flat T wave into inverted T wave, identification of ectopic rhythms, atrioventricular or intraventricular block.

### **7.5 Evaluation of changes in symptoms or signs**

- Markedly effective: clinical signs and symptoms disappear or 2 points lower relative to baseline (e.g. 3 points to 1 point);
- Effective: clinical signs and symptoms have been improved or 1 point lower relative to baseline (e.g. 3 points to 2 points, or 2 points to 1 point);

- Ineffective: clinical signs and symptoms remain unchanged;
- Worsening: clinical signs and symptoms become worse.

## 7.6 Use of nitroglycerin

- Withdrawal: complete withdrawal after treatment;
- Dose reduction: the number of doses decreased at least 50% after treatment;
- Unchanged: the number of doses decreased less than 50% after treatment.

## 8 ADVERSE EVENTS

### 8.1 Background information about drug-related safety issues

Based on the data from preclinical pharmacological and toxicological studies provided by the sponsor, evidence of XXK-related adverse reactions is not identified.

### 8.2 Monitoring and recording of adverse events

#### 8.2.1 Definition

**Adverse event (AE):** An AE is any untoward medical occurrence in a patient or clinical investigation subject administered a pharmaceutical product and that does not necessarily have a causal relationship with this treatment. An AE can therefore be any unfavorable and unintended sign (including an abnormal laboratory finding), symptom, or disease temporally associated with the use of a medicinal (investigational) product, whether or not related to the medicinal (investigational) product. Pre-existing conditions which worsen during a study are also to be reported as AEs.

**Serious Adverse Event (SAE):** A SAE is any experience that suggests a significant hazard, contraindication, side effect or precaution. It is any AE that at any dose fulfils at least one of the following criteria:

- is fatal;
- is life-threatening;
- required in-patient hospitalization or prolongation of existing hospitalization;
- results in persistent or significant disability/incapacity;
- is a congenital anomaly/birth defect;
- is medically significant or requires intervention to prevent one or other of the outcomes listed above.

**Adverse drug reaction (ADR):** An ADR is any unintended harm or injury associated

with the use of given medications at a normal dosage during normal use. In clinical trials of any new drug or any new usage of a certain drug, any unintended harm or injury that has a causal relationship to the use of the drug should also be considered as an ADR.

### **8.2.2 Recording**

For all AEs encountered during the clinical study, the following must be assessed and recorded on the adverse events form of the case report form (CRF): intensity, relationship to study drug, action taken regarding study drug, and outcome to date. All AEs, especially those for which the relationship to test drug is not “unrelated”, should be followed up until they have returned to baseline status or stabilized. The follow-up procedures could be performed in clinic visits or during hospitalization, or via home visit, telephone or mail, depending on the severity of AEs.

### **8.3 Severity of An AE**

**Mild:** events require minimal or no treatment and do not interfere with the subject’s daily activities.

**Moderate:** events result in a low level of inconvenience or concern with the therapeutic measures. Moderate events may cause some interference with functioning.

**Severe:** events interrupt a subject’s usual daily activity and may require systemic drug therapy or other treatment. Severe events are usually incapacitating.

### **8.4 Relationship to study drugs**

Attribution of an AE can be categorized as not related, unlikely related, possibly related, probably related, or definitely related to the study drugs.

**Not related:** The AE is clearly not related to the investigational agent/procedure. - i.e. Another cause of the event is most plausible; and/or a clinically plausible temporal sequence is inconsistent with the onset of the event and the study medication administration; and/or a causal relationship is considered biologically implausible.

**Unlikely related:** The AE is doubtfully related to the investigational agent/procedure.

**Possibly related:** The AE follows a reasonable temporal sequence from administration of the study drug/procedure, follows a known or expected response pattern to the suspected drug, but that could readily have been produced by a number of other factors.

**Probably related:** The AE is likely related to the investigational agent/procedure.

**Definitely Related:** The AE is clearly related to the investigational agent/procedure – i.e. An event that follows a reasonable temporal sequence from administration of the study drug, follows a known or expected response pattern to the suspected drug, that is confirmed by improvement on stopping and reappearance of the event on repeated exposure and that could not be reasonably explained by the known characteristics of the patient's clinical state.

### **8.5 Handling of SAEs**

All SAEs should be managed properly and timely, and recorded on the appropriate SAE CRF. Any AE considered serious by the investigator or which meets the aforementioned criteria must be submitted on a signed and dated SAE form to the sponsor, ethics review committee and relevant authorities within 24 hours of site awareness. And the sponsor should also inform all study sites of such SAEs in a timely manner to ensure subjects' safety in accordance with applicable laws and regulations.

Fatal or life-threatening events considered to be caused by the study drugs must be reported immediately to the sponsor and relevant authorities via telephone, fax, EMS or E-mail.

### **8.6 Opening and handling of emergency envelopes**

The emergency envelope provided along with each test drug in its package should only be opened in case of a serious complication or a serious adverse event, which is called emergency unblinding. Once unblinded, the patient should be withdrawn from the study and regarded as a dropout case. Information about when, where and why the emergency unblinding occurs as well as each personnel's signature should also be documented.

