### **3.7 Interim analysis**

One interim analyses will be conducted under blinding conditions after 1/2 of the total number of cases have completed the trial. The statistical results of interim analysis will be reported to the Data and Safety Monitoring Board and Implementation & Decision-making Committee, which will decide the subsequent arrangement and calculate the needed number of cases in the next stage of trial. If one group of treatment is terminated after the interim analysis, patients in this group may choose to crossover to continue with the trial or discontinue treatment and only report their safety information (considered as dropout cases).

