#### **4.5.3 Withdrawal/dropout criteria**

- Those who did not fulfill the eligibility criteria but were included by mistake;
- Those who fulfilled the eligibility criteria but did not take any study drug after randomization;
- Those with poor compliance that might interfere with the efficacy and safety evaluation;

- Those who experienced serious AEs, complications or special physiological changes, making it inappropriate to continue with the trial;
- Individual cases that were unblinded prematurely;
- Those who discontinued the trial voluntarily;
- Those who used any disallowed concomitant medication, especially those that had an obvious effect on the study drug and might interfere with the efficacy and safety evaluation;
- Those who discontinued or lost to follow-up for any other reasons or died during the trial;
- Those with incomplete data that might interfere with the efficacy and safety evaluation.

For all withdrawal/dropout cases, the potential reasons must be recorded. Patients who experienced any AE during the trial must be included in the statistical analysis of adverse drug reactions. Those who have taken the study drug for at least 1 week should be included in the statistical analysis of drug efficacy.

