### **12.3 Compliance enhancement**

The informed consent procedure is essential to ensure patients' compliance to treatment. The study drug, laboratory examinations, transportation and healthcare consultation will be provided by the sponsor free of charge.

Compliance rate is calculated by taking the amount of drug ingested divided by the amount the patient should have ingested and multiply by 100%. A compliance rate at 80%-120% defines good compliance; while that < 80% or > 120% defines poor compliance.

Patients should be asked to report all the concomitant medications while on study. Patients who have poor efficacy or poor compliance should be closely followed up.

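### Sections 8.6 and 4.5.3 take patients out of the study without separating stopped drug from ended follow-up, so their week-20 primary outcomes are not secured

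*Protocol*

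**What the plan says.** - **Section 8.6** reserves the emergency envelopes for a serious complication or serious adverse event, and continues: "Once unblinded, the patient should be withdrawn from the study and regarded as a dropout case". The rule has no exception. Section 3.5 also describes emergency unblinding but does not mention withdrawal.
- **Section 4.5.3** has a single withdrawal/dropout list. It includes "Individual cases that were unblinded prematurely", "Those who used any disallowed concomitant medication, especially those that had an obvious effect on the study drug", "Those who experienced serious AEs, complications or special physiological changes, making it inappropriate to continue with the trial" and "Those with poor compliance that might interfere with the efficacy and safety evaluation". The last two are conditional. Voluntary discontinuation, loss to follow-up and death are in the same list. For all of these the section asks that the reason be recorded. It also puts anyone with at least one week of study drug into the efficacy analysis.
- **Section 4.5.5** tells investigators to record "the efficacy and safety parameters at and after discontinuation" and to complete the CRF of withdrawn patients. It names no visit and no time point.
- **Section 6.2** defines angina-free over the 20-week treatment phase, scored at weeks 2, 4, 6, 8 and 20. ECG improvement is defined after 20 weeks, with ECGs at weeks 0, 8 and 20.
- **Section 15** (flowchart) has visits at weeks 0, 2, 4, 6, 8 and 20, and no early-termination or post-withdrawal visit.
- **Section 11.1.1** applies LOCF to patients who do not complete the study.

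**The concern.** Stopping study drug and leaving follow-up are different events. A patient can stop the drug, or be unblinded, and still have a week-20 ECG and angina score. Sections 8.6 and 4.5.3 treat the two as one. Section 4.5.5 points the other way but gives sites nothing to schedule. One site could end visits under 8.6, another could go on collecting efficacy data under 4.5.5, and both could say that they followed the protocol.

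The reasons for removal are plausibly tied to the outcome. A patient who takes another angina drug, has a serious complication or stops taking study medication is unlikely to resemble the average completer. If removals also differ between groups, the treatment comparison is biased. The loss arises at the site, so no later analysis rule can supply an ECG that was not taken.

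**Working it through.** **Step 1. Set the instructions side by side.**

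| Section | Status of the patient | Data asked for afterwards |
|---|---|---|
| 8.6 | withdrawn from the study, dropout | not stated |
| 4.5.3 | withdrawal/dropout | the reason |
| 4.5.5 | discontinued or withdrawn | efficacy and safety, no visit named |
| 8.2.2, 8.7 | any patient with an adverse event | follow-up of that event |
| 15 | not addressed | no visit after withdrawal |

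Only 4.5.5 asks for later efficacy data, and no scheduled assessment carries it out for a patient classed as withdrawn.

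**Step 2. What LOCF has to work with if visits end at withdrawal** (schedule from sections 6.2 and 15).

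| Patient leaves | Last scheduled angina score | Last scheduled ECG |
|---|---|---|
| between weeks 2 and 4 | week 2 | week 0 |
| between weeks 6 and 8 | week 6 | week 0 |
| between weeks 8 and 20 | week 8 | week 8 |

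A patient who scores none at week 2 and then leaves can be carried forward to week 20 as angina-free. Before week 8 there is no scheduled ECG after baseline, so LOCF uses the baseline tracing or has nothing to use. After week 8, a tracing taken 20 − 8 = 12 weeks before the endpoint stands in for it.

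**Step 3. Size.** The protocol gives no rate for unblinding, disallowed medication, qualifying serious events or qualifying non-compliance, so there is no plan figure to reproduce. The loss rates below are assumptions.

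Inputs: angina-free rates of 30% (trial) and 20% (control) from section 3.2, a true difference of 10.0 points. Assume that every removed patient would have been a failure and that only completers are analysed. With a fraction d removed, the completer rate is p / (1 − d).

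| Assumed loss, trial v control | Trial | Control | Difference (points) |
|---|---|---|---|
| 5% v 5% | 0.30/0.95 = 31.6% | 0.20/0.95 = 21.1% | 10.5 |
| 10% v 5% | 0.30/0.90 = 33.3% | 0.20/0.95 = 21.1% | 12.3 |
| 15% v 5% | 0.30/0.85 = 35.3% | 0.20/0.95 = 21.1% | 14.2 |
| 5% v 10% | 0.30/0.95 = 31.6% | 0.20/0.90 = 22.2% | 9.4 |

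Differences are taken before rounding. The bias can go either way, depending on which group loses more.

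**Step 4. Power, for comparison.** With 736/2 = 368 per group, 30% v 20% and a two-sided 0.05 test, power is 88.1%. With 10% random loss (368 × 0.90 ≈ 331 per group) it is 84.6%. If the lost 10% count as failures (27% v 18% in 368 per group) it is 83.4%. Power falls only modestly; bias is the main issue.

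**The case against.** The best reply is that 4.5.5 already covers these patients. It applies to discontinuation in any case, asks for efficacy as well as safety, and requires the CRF of withdrawn patients to be completed. Section 14.4 repeats the CRF duty for patients who do not finish. Neither 8.6 nor 4.5.3 forbids later data. A patient who stops between weeks 8 and 20 should have efficacy recorded at that point, and one stopped for worsening is classed as ineffective. All of this stands, and it is why the outcomes are *not secured* rather than *lost*. It does not close the gap, because recording at discontinuation is not a week-20 assessment and nothing in 4.5.5 fixes one.

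A reader might infer more than the documents support:

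- *That every patient with a serious event or poor compliance leaves.* Both criteria in 4.5.3 are conditional. Only the unblinding rule in 8.6 is without condition.
- *That section 3.7 restricts anyone who stops to safety data.* It concerns only the patients of a group terminated after the interim analysis, and section 3.2 shows that the interim led to expansion.
- *That section 12.3 contradicts 4.5.3.* It says "Patients who have poor efficacy or poor compliance should be closely followed up". A patient can be followed closely and later meet the 4.5.3 condition.
- *That about 19% of outcomes are at risk.* The initial step from 465 to 576 gives 111/576 = 19.3%. That allowance is superseded, covers dropout for any reason and includes rounding for site blocks. The re-estimate to 736 assumes low dropout.

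Nor do the documents show that removals differ by group. Some 4.5.3 criteria, such as enrolment by mistake, need have nothing to do with outcome.

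**Conclusion.** The point holds in a limited form. Sections 8.6 and 4.5.3 remove certain patients from the study without saying whether follow-up continues. Section 4.5.5 asks for later efficacy data without a visit, and the flowchart provides none. Week-20 data for both primary endpoints are therefore left to each site's reading, and the planned LOCF replaces missing values with earlier ones.

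The size is unknown. The 12.3-point example rests on three assumptions: losses of 10% and 5%, failure in every removed patient, and an analysis of completers only. The last is not the planned full-analysis-set approach, so the figure shows how unequal loss could act and does not forecast this trial's bias. That removal is related to outcome is plausible from the listed criteria but is not demonstrated. The change is worth making because it is cheap and cannot be replaced by a later analysis rule.

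**What to change.** Reconcile 8.6 and 4.5.3 with 4.5.5, on data collection only:

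1. In 4.5.3, distinguish stopping study drug from withdrawing consent to follow-up.
2. State once, and refer to it from 8.6 and 4.5.5, that a randomised patient who stops study drug or is unblinded, and has not withdrawn consent, is asked to attend the remaining scheduled visits. The minimum is week 20, with angina score, 12-lead ECG, SAQ and adverse events.
3. Flag data collected off treatment or after unblinding, and deal with them by exclusion from the per-protocol set.

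When treatment stops and when the blind may be broken are for the sponsor to settle; nothing here proposes a rule.

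Cost: a wording amendment, with the ethics approval that section 18 requires. No new visit or procedure is added to the schedule, although some patients would attend visits that they might otherwise have missed. The downside is that some outcomes will be observed off treatment or by people who know the allocation, which is why the flag is needed.
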